### **3.9 Data collection methods**

The data collection will occur in the selected districts in Selangor, Malaysia, within a given time frame. The questionnaire will be distributed to selected respondents in the selected Food Handler Training School. All participants who agree to participate in the study will be consented by agreeing to the agreement statement prior study begins. The questionnaire will be given in the Google Form format for the participants to access the form with the response collected immediately upon completion before and immediately after training. The participants will be contacted after one-month post-training for the reassessment of the KAP score. If the accessibility of the Google Form is not available, the same questionnaire in the hardcopy format will be given and collected on the same day at all mentioned events.

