### **3.10 Data analysis**

The collected data and will be analyzed using IBM Statistical Package for Social Science (SPSS) version 25 involving descriptive and inferential statistics. Descriptive statistics will be used to describe the characteristics of participants. Whilst, the descriptive analysis for continuous variables with mean, mode, median and percentage will be analyzed.

The bivariate analysis of Chi-square will be used to measure associations between two categorical variables. A generalized Linear Mixed Model (GLMM) then will be conducted to determine the effects of sociodemographic factors (age, gender, ethnicity, level of education), socioeconomic (employment status, household income), working experience (duration) and previous training (training attended) on KAP on occupational safety and health at food premises among food handlers pre and post intervention within and between study groups.

In further analysis, the effects of SCT constructs component as the base of the theory-based intervention module which is behavior, individual and environment factors on KAP on occupational safety and health at food premises among food handlers pre and post intervention within and between study groups will be determined.

The effects that are going to be determined is fixed and random effects. The fixed effect is factors that the only level under consideration are continued in coding those effects. For example, both male and female genders are included in the factor sex; other examples as different ethnicities are included in the factor ethnicity group. On the other hand, the random effect is the factors where its effects are random, where they are assumed to be drawn randomly from a distribution during the data-generating process. In this study, the study sample is a random sample of the target population of food handlers at food premises and the study needs to measure KAP score of the food handlers a few times.

GLMM can incorporate both fixed and random effects. Individual's response at baseline (intercept) is allowed to differ across subjects by releasing the random effect of intercept. The change in response over time is also allowed to differ across subjects by releasing the random effect of a linear slope. By adding the random effects in the model, GLMM provides estimated parameters (fixed effect) and individual variability of these parameters around the population trend (Ellison, 2017).

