| Post-intervention                                                         |               |    |           |
| 1-month                                                                   |               |    |           |

\*Repeated measure ANOVA

\*\*Bonferroni adjustment

\*\*\*Significant at  $p < 0.05$

Table F. Fixed Coefficient of variables for self efficacy on occupational safety and health at food premises

| Variable          | Coefficients | Std. Error | t | p-value | 95% CI |       |
|-------------------|--------------|------------|---|---------|--------|-------|
|                   |              |            |   |         | Lower  | Upper |
| Group      |              |            |   |         |        |       |
| Intervention      |              |            |   |         |        |       |
| Control           |              |            |   |         |        |       |
| Time       |              |            |   |         |        |       |
| Baseline          |              |            |   |         |        |       |
| Post-intervention |              |            |   |         |        |       |
| 1-month           |              |            |   |         |        |       |
| Education  |              |            |   |         |        |       |
| Primary           |              |            |   |         |        |       |
| Secondary         |              |            |   |         |        |       |
| Tertiary          |              |            |   |         |        |       |

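### Section 3.10 puts a random linear slope on three unevenly spaced scores, which can misstate standard errors, and does not say how time is coded for knowledge, attitude and practice

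*Combined protocol and SAP*

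**What the plan says.** Section 3.10 describes a generalized linear mixed model with two person-level random effects. For the intercept: "Individual's response at baseline (intercept) is allowed to differ across subjects by releasing the random effect of intercept". For time: "The change in response over time is also allowed to differ across subjects by releasing the random effect of a linear slope". It then separates the fixed part from the random part: "GLMM provides estimated parameters (fixed effect) and individual variability of these parameters around the population trend". It does not say how the fixed effect of time is coded.

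Section 3.9 sets three assessments. The first two are "with the response collected immediately upon completion before and immediately after training". For the third, "The participants will be contacted after one-month post-training for the reassessment of the KAP score".

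Objective 4 (Section 1.5.2) asks for comparisons at the end of training and at one month. The only table of model coefficients shown is Table F in Section 4.1, "Fixed Coefficient of variables for self efficacy on occupational safety and health at food premises". It lists Time as baseline, post-intervention and 1-month. Self-efficacy is neither a primary nor a secondary outcome in Section 3.6.1, which names knowledge and attitude as primary and practice as secondary. No matching table is shown for those three.

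**The concern.** The first two scores bracket the training, and the third comes a month later. Whatever the training does to a person's score should show as a jump at the second assessment, followed by retention or fading. People will differ in the size of the jump and in how much they keep. A random straight line per person is a poor description of that variation.

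The random part determines the model-based standard errors. If it has the wrong shape, the tests and confidence intervals for the two comparisons in Objective 4 can be off, the end-of-training one in particular. Because Section 3.10 is silent on the fixed coding of time for knowledge, attitude and practice, the analyst also has to supply part of the main model.

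**Working it through.** The plan gives no SD, correlation or standard error for these scores, so there is no figure of its own to reproduce. All covariances below are assumptions. The calculation is large-sample, with complete data, visits coded 0, 1, 2 and the school effect left out.

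1. **Means.** Assume true arm differences of 0, 1.0 and 0.5 SD at the three assessments. With three-level time crossed with group, plus a random intercept and linear slope (intercept variance 0.5, residual variance 0.5, slope variance 0 or 0.3), generalised least squares returns 0, 1.0 and 0.5. There is no bias.

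2. **What the random part imposes.** Let g be the slope variance and s² the residual variance. The model implies:
   - Var(end − baseline) = g + 2s²
   - Var(one month − end) = g + 2s²
   - Var(one month − baseline) = 4g + 2s²

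   So the first two variances are forced to be equal, and the third cannot be smaller than either. A step followed by retention or fading need not satisfy this.

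3. **First example.** SDs 2.0, 1.2, 1.7; correlation 0.3 between baseline and end of training, 0.6 between end of training and one month.
   - True Var(end − baseline) = 4.00 + 1.44 − 2(0.3)(2.0)(1.2) = 4.00
   - True Var(one month − end) = 1.44 + 2.89 − 2(0.6)(1.2)(1.7) = 1.88
   - The fit replaces both by their average, 2.94
   - SE ratios (model/true): √(2.94/4.00) = 0.86 and √(2.94/1.88) = 1.25. The baseline-to-one-month ratio is 1.00.

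4. **Second example.** Equal SDs of 1; correlations 0.3 (baseline, end), 0.6 (baseline, one month), 0.4 (end, one month).
   - True variances of the differences: 2(1 − 0.3) = 1.4; 2(1 − 0.6) = 0.8; 2(1 − 0.4) = 1.2
   - The slope variance is fitted as zero, so all three are pooled: (1.4 + 0.8 + 1.2)/3 = 1.133
   - SE ratios: √(1.133/1.4) = 0.90; √(1.133/0.8) = 1.19; √(1.133/1.2) = 0.97

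5. **Range.** The model covariance V was fitted to each true covariance S by minimising log|V| + tr(V⁻¹S). Five patterns were used: the types in steps 3 and 4, and person-specific gains with 50% or 80% retained. They gave end-of-training ratios of 0.91, 0.90, 0.86, 0.85 and 0.86. A further set with person-specific gains and 0-100% retained gave an end-of-training SE 7-11% too small, and other contrasts from 7% too small to 21% too large. Together: 7-15% too small at end of training; later contrasts from 7% too small to 25% too large.

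6. **Effect on the test.** Actual level = 2{1 − Φ(1.96 × ratio)}. Ratio 0.93 gives 6.8%; ratio 0.86 gives 9.2%. The most extreme pattern gives 9.4% before its ratio is rounded to 0.85.

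7. **Patterns with little or no error.** Compound symmetry at 0.5 and AR(1) at 0.6 give ratios of 1.00 throughout. Equal SDs with correlations 0.50, 0.45, 0.55 give 0.975 at end of training. SDs 1, 1.1, 1.2 with correlation 0.5 give 1.045, which is conservative.

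8. **If time were also linear in the means.** Let the true arm differences be 0, D and rD.
   - Visits coded 0, 1, 2: the slope is (−1·0 + 0·D + 1·rD)/2 = rD/2, so the fitted end-of-training change is 0.50D, 0.25D or 0 for r = 1, 0.5 or 0.
   - Days 0, 0, 30: the line passes through 0.5D at day 0 and rD at day 30. The fitted end-of-training change is 0 and the one-month change is (r − 0.5)D.

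**The case against.** A reader might infer from the linear-slope sentence that Section 3.10 models average change as a straight line, so that the training effect at each follow-up is misstated as in step 8. The documents do not support that. The sentence concerns how individuals differ, and the next one sets the fixed effect apart from "individual variability of these parameters around the population trend". Table F codes Time in three levels, Tables B to E report the three times separately, and Objective 4 asks for comparisons at two times. Three-level fixed time with a random slope is a coherent model. Even under linear means, step 8 concerns change from baseline. Coded in days, the fitted arm difference at one month would be rD, which is correct. Coded 0, 1, 2 with r = 1, the fitted difference at end of training would be 67% of D, not 50%. So the bias is a possibility that the silence on coding leaves open, not a feature of the plan.

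It can also be said that the standard-error problem depends on the patterns chosen. That stands: step 7 shows plausible covariances with no error, a small one, or a conservative one. The second example also needs the baseline score to correlate more with the one-month score than with the score taken right after training. Finally, the calculation omits the school effect, although allocation is by cluster.

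The objection does not remove the stated random part. Section 3.10 commits to it, and nothing in the plan justifies a line for this schedule.

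**Conclusion.** The point holds as a conditional standard-error problem together with an unstated coding of time. With three-level time crossed with group, the arm differences are not biased. Under step-type covariances the end-of-training standard error is about 7-15% too small and the 5% test runs at roughly 7-9%; the later contrasts range from about 7% too small to 25% too large. Under compound symmetry there is no error. These ranges cover the assumed patterns and are not bounds. They rest on visits coded 0, 1, 2, complete data, a large sample and no school effect. Misstated effects would follow only if time were also linear in the means, which the plan neither states nor rules out for knowledge, attitude and practice. Moderate severity; a cheap improvement.

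**What to change.** In Section 3.10, for knowledge, attitude and practice:

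- enter time as a three-level factor (baseline, end of training, one month), as Table F does, crossed with group;
- replace the person-level random intercept and linear slope with an unstructured 3x3 covariance for a participant's repeated scores, and delete the sentences on the linear slope and the population trend;
- report the arm contrast separately at end of training and at one month, and add a coefficient table for each of the three outcomes.

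The cost is a change of wording in the analysis section. Standard mixed-model software fits this model. It estimates six covariance parameters instead of four. The change does not supply the school-level effect, which Section 3.10 also does not name and which is a separate matter.

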### 3.11 Quality control

The instrument will test for validity and reliability as follows:

- I. Face validity: A pre-test will be conducted among ten food handlers' staffs from Hospital Perubatan Universiti Putra Malaysia. The questionnaire will be revised based on their feedback and comment.
- II. Content validity: The questionnaire will be discussed among two specialists in Public Health Medicine for assurance.
- III. Reliability: A test-retest of the questionnaire will be conducted among adult at the age of 19-65 at the selected Food Handler Training in Selangor, Malaysia. The data will be assessed using kappa statistics (K).

### 3.12 Ethical approval

Ethical approval will be obtained from the Ethics Committee for Research involving Human Subjects of University Putra Malaysia (JKEUPM). A consent form from each participant will be obtained upon agreement to participate in the study before answering the questionnaire.

As for practice, there will be suggested items rated as five-point Likert-item questions with the responses of never, rarely, sometimes, often, and always, each weighing 1–5 scores, respectively. Their self-reported practice scores of them were classified as weak (<40), acceptable (40–50), and desirable (51–60). In addition, the observed practices presented a slight correlation with the self-reported practices in a previous study (Cunha et al., 2019).

The last section included three questions about the participants’ source of information, their need for education, and how they can increase their knowledge

of this issue. Also, they were asked to comment on (a) What they most liked about the course, (b) How it could be improved, and (c) What they will do differently at work as a result of their training.

## CHAPTER 4

## RESULTS

## 4.1 Results Dummy Table

Table A. Baseline comparison of sociodemographic, socioeconomic, working experience, and training attendance characteristics between-group (n=).

|                                       | Group median (IQR) / n (%) |              | Statistical Test | p-value |
|---------------------------------------|----------------------------|--------------|------------------|---------|
|                                       | Control                    | Intervention |                  |         |
| Age (years)                    |                            |              |                  |         |
| Gender                         |                            |              |                  |         |
| Male                                  |                            |              |                  |         |
| Female                                |                            |              |                  |         |
| Ethnicity                      |                            |              |                  |         |
| Malay                                 |                            |              |                  |         |
| Chinese                               |                            |              |                  |         |
| Indian                                |                            |              |                  |         |
| Others                                |                            |              |                  |         |
| Educational status             |                            |              |                  |         |
| Primary school                        |                            |              |                  |         |
| Secondary school                      |                            |              |                  |         |
| SPM/STPM/Matriculation/Diploma        |                            |              |                  |         |
| First degree                          |                            |              |                  |         |
| Second degree and third degree        |                            |              |                  |         |
| No formal education                   |                            |              |                  |         |
| Employment status              |                            |              |                  |         |
| Government servant                    |                            |              |                  |         |
| Private company                       |                            |              |                  |         |
| Self-employed                         |                            |              |                  |         |
| Student                               |                            |              |                  |         |
| Unemployed                            |                            |              |                  |         |
| Monthly individual income (RM) |                            |              |                  |         |
| Monthly household income (RM)  |                            |              |                  |         |
| Previous working experience    |                            |              |                  |         |
| Yes                                   |                            |              |                  |         |
| No                                    |                            |              |                  |         |
| Length of experience (years)   |                            |              |                  |         |
| Previous training attendance   |                            |              |                  |         |
| Yes                                   |                            |              |                  |         |
| No                                    |                            |              |                  |         |
| Typhoid injection status       |                            |              |                  |         |
| Yes                                   |                            |              |                  |         |
| No                                    |                            |              |                  |         |

Table B. Between-group difference of total score of self-efficacies, behavioral capacity, and supportive working environment on occupational safety and health at food premises.

|                                                          | Group median (IQR) |                   |         |
|----------------------------------------------------------|--------------------|-------------------|---------|
|                                                          | Baseline           | Post-intervention | 1-month |
| The total score of self efficacies                |                    |                   |         |
| Control                                                  |                    |                   |         |
| Intervention                                             |                    |                   |         |
| Man-Whitney U Test                                       |                    |                   |         |
| p-value                                           |                    |                   |         |
| The total score of behavioral capacity            |                    |                   |         |
| Control                                                  |                    |                   |         |
| Intervention                                             |                    |                   |         |
| Man-Whitney U Test                                       |                    |                   |         |
| p-value                                           |                    |                   |         |
| The total score of supportive working environment |                    |                   |         |
| Control                                                  |                    |                   |         |
| Intervention                                             |                    |                   |         |
| Man-Whitney U Test                                       |                    |                   |         |
| p-value                                           |                    |                   |         |

Significant at  $p < 0.05$

Table C. Within intervention group difference of total score of self-efficacies on occupational safety and health at food premises.

| Self-efficacy on occupational safety and health at food premises | Mean $\pm$ SD | F* | p-value** |
|------------------------------------------------------------------|---------------|----|-----------|
| Within Intervention group.                                       |               |    |           |
| Baseline                                                         |               |    |           |
| Post-intervention                                                |               |    |           |
| 1-month                                                          |               |    |           |
| Within Control Group                                             |               |    |           |
| Baseline                                                         |               |    |           |
| Post-intervention                                                |               |    |           |
| 1-month                                                          |               |    |           |

\*Repeated measure ANOVA

\*\*Bonferroni adjustment

\*\*\*Significant at  $p < 0.05$

Table D. Within intervention group difference of total score of behavioral capacity on occupational safety and health at food premises.

| Behavioral capacity on occupational safety and health at food premises | Mean $\pm$ SD | F* | p-value** |
|------------------------------------------------------------------------|---------------|----|-----------|
| Within Intervention group.                                             |               |    |           |
| Baseline                                                               |               |    |           |

|                      |  |  |  |
|----------------------|--|--|--|
| Post-intervention    |  |  |  |
| 1-month              |  |  |  |
| Within Control Group |  |  |  |
| Baseline             |  |  |  |
| Post-intervention    |  |  |  |
| 1-month              |  |  |  |

\*Repeated measure ANOVA

\*\*Bonferroni adjustment

\*\*\*Significant at  $p < 0.05$

Table E. Within intervention group difference of total score of supportive working environment on occupational safety and health at food premises.

| Supportive environment on occupational safety and health at food premises | Mean $\pm$ SD | F* | p-value** |
|---------------------------------------------------------------------------|---------------|----|-----------|
| Within Intervention group.                                                |               |    |           |
| Baseline                                                                  |               |    |           |
| Post-intervention                                                         |               |    |           |
| 1-month                                                                   |               |    |           |
| Within Control Group                                                      |               |    |           |
| Baseline                                                                  |               |    |           |
| Post-intervention                                                         |               |    |           |
| 1-month                                                                   |               |    |           |

\*Repeated measure ANOVA

\*\*Bonferroni adjustment

\*\*\*Significant at  $p < 0.05$

Table F. Fixed Coefficient of variables for self efficacy on occupational safety and health at food premises

| Variable          | Coefficients | Std. Error | t | p-value | 95% CI |       |
|-------------------|--------------|------------|---|---------|--------|-------|
|                   |              |            |   |         | Lower  | Upper |
| Group      |              |            |   |         |        |       |
| Intervention      |              |            |   |         |        |       |
| Control           |              |            |   |         |        |       |
| Time       |              |            |   |         |        |       |
| Baseline          |              |            |   |         |        |       |
| Post-intervention |              |            |   |         |        |       |
| 1-month           |              |            |   |         |        |       |
| Education  |              |            |   |         |        |       |
| Primary           |              |            |   |         |        |       |
| Secondary         |              |            |   |         |        |       |
| Tertiary          |              |            |   |         |        |       |

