### **1.5.2 SPECIFIC OBJECTIVE**

The specific objectives of this study are:

1. To describe the baseline sociodemographic, socioeconomic, working experience, training attendance, and means KAP score of food handlers.
2. To develop and implement a theory-based intervention module for food handlers in Selangor, Malaysia.
3. To evaluate the effectiveness of the SCT constructs as the main framework of the intervention module in improving KAP among food handlers between the intervention and control group.

4. To describe and compare the effectiveness of the TRIM-OSH on the change of knowledge, attitude and practice compared to standard training among food handlers between and within groups at the end, and one-month post training, after controlling for covariates.

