## 1.6 RESEARCH HYPOTHESIS

The research hypothesis of this study is:

- H1:** The sociodemographic, socioeconomic, working experience, and training attendance characteristics of the intervention and control groups would be the same.
- H01:** There is no significant differences in the sociodemographic, socioeconomic, working experience, and training attendance characteristics of the intervention and control groups.
- H2:** The KAP on occupational safety and health at food premises of the intervention and control groups at the baseline would be the same.
- H02:** There is no significant differences in the KAP on occupational safety and health at food premises of the intervention and control groups at the baseline.
- H3:** The SCT constructs as the main framework of the intervention module is effective in improving KAP among food handlers between the intervention and control group.
- H03:** The SCT constructs as the main framework of the intervention module have no significant effect in KAP among food handlers between the intervention and control group.
- H4:** The TRIM-OSH effectively improves KAP on occupational safety and health at food premises among food handlers.

**H04:** There is no significant differences in the KAP on occupational safety and health at food premises of the intervention and control groups at post-intervention.

## CHAPTER 2

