All results of log-transformed data considered underlying data transformation in result interpretation. The confidence interval will be set at 95% for mean estimations. The level of significance, alpha ( $\alpha$ ), will be set at 0.05. A p-value of less than 0.05 pertained to the decision rule. The dependent variables measured in this study are the outcome (primary and secondary) and effectiveness of the SCT constructs as the base of theory-based intervention module in occupational safety and health training among food handlers.

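### H3 has no decisive construct, time point or test, its outcome (KAP) is not what Table B tests, and Table B's six between-arm tests are unadjusted at 0.05

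*Combined protocol and SAP*

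**What the plan says.** Section 1.6 states H3 as "The SCT constructs as the main framework of the intervention module is effective in improving KAP", as a comparison of the two arms, and pairs it with a null hypothesis H03. It serves specific objective 3 in section 1.5.2.

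Section 3.10 names the "effectiveness of the SCT constructs as the base of theory-based intervention module in occupational safety and health training among food handlers" as a dependent variable beside the primary and secondary outcomes. The significance level "will be set at 0.05. A p-value of less than 0.05 pertained to the decision rule". The same section introduces the SCT work as a further analysis: effects of behaviour, individual and environment factors on KAP. Section 3.6.1 lists no SCT construct among either the primary outcomes (knowledge, attitude) or the secondary ones (practice, maintenance).

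In section 4.1, Table B is titled "Between-group difference of total score of self-efficacies, behavioral capacity, and supportive working environment on occupational safety and health at food premises". For each of three constructs it has columns for baseline, post-intervention and 1 month, a row for the "Man-Whitney U Test" and a p-value, with 0.05 as the threshold and no adjustment note. Tables C, D and E give repeated-measures ANOVA within each arm over time, with the footnote "Bonferroni adjustment". Table F gives model coefficients for self-efficacy by group, time and education.

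**The concern.** H3 is one statement, but the plan offers several analyses that could be read as answering it and does not say which one does. Table B alone yields several between-arm p-values for the one hypothesis, each judged at 0.05, with no statement of whether one positive result is enough or all are needed. A report could then cite a single significant construct at a single time as proof that the SCT framework works, even if the other constructs or the other time disagree.

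The Bonferroni footnote under Tables C to E makes this easier to miss. It suggests error control, but it protects only comparisons over time inside one arm. A change within the intervention arm says nothing about a difference from control.

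There is also a mismatch of variable. H3 is about KAP, whereas Table B is about construct scores. A significant Table B cell would show that a construct moved, not that KAP improved.

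**Working it through.** **Which analysis answers H3?**

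| Place | Variable | Comparison | Multiplicity |
|---|---|---|---|
| H3, section 1.6 | KAP | between arms | none stated |
| Section 3.10, further analysis | KAP, by SCT factors | within and between arms | none stated |
| Table B | three construct scores | between arms, Mann-Whitney | none |
| Tables C to E | construct scores | within arm, over time | Bonferroni |
| Table F | self-efficacy | group, time, education coefficients | none stated |

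No row is named as the one that decides H3, and the row with between-arm tests (Table B) does not use H3's outcome.

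**Number of tests.** Table B has 3 constructs × 3 times = 9 p-values. Baseline cannot show an effect of training, which leaves 3 × 2 = 6. The two later times match objective 4, which looks "between and within groups at the end, and one-month post training, after controlling for covariates".

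**Chance of at least one false positive among the six.** The plan gives no such figure, so there is none to reproduce. Inputs: 0.05 per test (section 3.10). Assumptions: two-sided tests, each valid, all null hypotheses true, a common correlation ρ between test statistics. The plan gives neither sidedness nor correlation, so ρ is varied.

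- Independent tests, either direction: 1 − 0.95⁶ = 1 − 0.735 = 26.5%.
- Independent tests, favouring the intervention only (2.5% each): 1 − 0.975⁶ = 1 − 0.859 = 14.1%.
- Correlated tests, either direction, with c = 1.96: 1 − ∫ φ(u) [Φ((c − √ρ u)/√(1−ρ)) − Φ((−c − √ρ u)/√(1−ρ))]⁶ du. For the favouring-only column, the second Φ term is dropped.

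| ρ | Either direction | Favouring the intervention |
|---|---|---|
| 0 | 26.5% | 14.1% |
| 0.3 | 24.1% | 12.2% |
| 0.5 | 20.7% | 10.4% |
| 0.7 | 16.4% | 8.2% |
| 0.8 | 13.9% | not computed |

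**Checks.** The documents give both 139 and 240 participants, so Mann-Whitney tests were simulated with 70 and with 120 per arm at ρ = 0.5. The either-direction result was 20.6% and 20.7%. Letting the correlation between constructs and the correlation between times vary separately from 0.3 to 0.7 gave 17.7% to 24.8%.

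**If all six had to be significant**, the chance of a false claim would be at most 5%.

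**Validity of each test.** Mann-Whitney treats participants as independent, but the trial randomizes clusters. With 12 per cluster (section 3.6) and an assumed ICC of 0.01 to 0.10, the design effect is 1 + 11 × ICC = 1.11 to 2.10. The real per-test error is 2Φ(−1.96/√1.11) = 6.3% to 2Φ(−1.96/√2.10) = 17.6%. On that assumption, six tests at ρ = 0.5 give 25% to 57%. The plan states no ICC, so this shows only that the table above may be too low.

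**After the change.** Three constructs at one time, unadjusted: 1 − 0.95³ = 14.3% if independent, 12.5% at ρ = 0.5. With Holm the smallest p-value must be below 0.05/3 = 0.0167. The chance of any false positive when all three null hypotheses are true is then 4.9% and 4.5%, given valid tests.

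**The case against.** The best reply is that the SCT work was never meant to carry a claim of its own. The plan does not call H3 confirmatory, section 3.6.1 leaves the constructs out of both outcome lists, and section 3.10 introduces them as further analysis. That stands as a point about ambiguity: a reader who infers a declared confirmatory claim goes beyond the text. It does not settle the matter, because H3 and H03 are set out in the same form as H4 and H04 and fall under the same p-value rule.

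Nor is it right to infer that the plan names no construct, time or test. Table B names three constructs, three times and the Mann-Whitney test. What is missing is a statement of which is decisive.

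The any-of-six reading is also only one way to fill the gap. No passage states it, and the all-must-succeed reading would not inflate the error at all. The percentages are therefore conditional on that reading.

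A reader might take 21% as the trial's false-claim rate. It is not a figure from the plan. It needs an assumed correlation of 0.5 and counts results in either direction, whereas H3 claims improvement. Counting only favourable results roughly halves it.

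Finally, one could count nine further tests in section 3.10 (three factors on three KAP scores). That count is inferred. The text would fit a joint model for each score equally well, so no error rate is claimed for it here.

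**Conclusion.** The point holds as a gap in specification. H3 is a formal hypothesis under a p below 0.05 rule, with no decisive construct, time point or test, and its outcome differs from the variable in Table B. The six post-training between-arm tests carry no adjustment, and the only correction shown applies to within-arm comparisons that cannot decide H3.

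If one significant cell is accepted as support, the chance of at least one false positive is about 14% to 27% in either direction (correlation 0.8 to 0), or about 10% to 14% in favour of the intervention (correlation 0.5 to 0) against a nominal 2.5%. This rests on the any-of-six reading, an assumed correlation and valid individual tests. The last is doubtful under cluster randomization, and the error from that source would be upward. The multiplicity calculation concerns only the SCT claim, not H4 or the KAP outcomes, and it calls for a change of wording rather than of design.

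**What to change.** Preferred: in sections 1.5.2, 1.6 and 3.10, label objective 3, H3 and the construct-on-KAP analyses as exploratory, giving information on mechanism with no claim of effectiveness. Label Tables B to F the same way. Reword H3 so that it names the variable actually tested.

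If H3 is kept as a formal claim, name one time point in advance and test the three between-arm construct contrasts there with Holm at an overall two-sided 0.05. Those contrasts need an analysis that respects the clusters, or Holm will not hold 5%. Report the other time point descriptively, and do not use the within-arm p-values in Tables C to E to support H3. Testing H3 only after H4 succeeds is not available as things stand, because H4 has no stated success rule.

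Cost: edits to the text and table footnotes. The SCT claim becomes exploratory, or slightly harder to reach. No new data are needed.
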